### Methods for additional analyses (e.g. subgroup analyses) {20b}

No additional analyses were performed.

### Methods in analysis to handle protocol nonadherence and any statistical methods to handle missing data {20c}

The loss to follow-up rate will be reduced by adherence to the strategies described above. The sample size is calculated to accommodate a loss to follow-up rate of 15% without affecting statistical power.

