## Introduction

### Background and rationale {6a}

IPMRCT results in severe shoulder dysfunction and shoulder instability. SCR and bridging patches have been increasingly used to treat IPMRCT [1, 2]. In the SCR technique, the patch graft is fixed on the glenoid in the medial direction and on the footprint of the rotator cuff in the lateral direction. SCR technique was introduced as an innovative treatment for MRCT in 2013 [1] and achieved a long-term successful outcome [2]. SCR restored superior glenohumeral joint stability and then improved shoulder joint function [1, 3]. Retear rates were seen with partial cuff repairs (45%), graft interposition (21%) and SCR (21%), respectively [3]. As a whole, SCR was a validated, safe option compared with partial repair or simply physiotherapy. SCR was an inexpensive option too compared with reverse shoulder arthroplasty. However, SCR did not restore the anatomy or dynamic function of the SSP tendon. Bridging techniques with different patches that mimic the anatomy of the SSP tendon have been reported [2, 4]. However, this technique should be used carefully because of the high retear rate associated with the patch graft-tendon interface, the poor mechanical properties of allogenic grafts and the possibility of inflammation [4]. The STR technique using the autogenous fascia latas (FL) was recently introduced to treat IPMRCT [5]. The technique achieved a stable anatomic and dynamic reconstruction of the SSP tendon with fascia-muscle fusion. It was hypothesized that STR would have better clinical outcomes than SCR. However, there are still no reports of the clinical outcomes.

The intention of this study was to evaluate the clinical efficacy of STR for the treatment of IPMRCT in a prospective randomized controlled study to provide evidence-based medical evidence for its extensive development.

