### Sample size {14}

Sample size calculation for ASES score analysis was performed with an expected standard deviation (SD) of 5.8, a significance level at 5% and power of 0.90 and resulted in 25 participants in each group (50 participants with allowance for 15% drop-out).

In our previous research on postoperative ASES scores of SCR, the score was 87.6 ± 5.8 at the latest follow-up. The best ASES result published by Mihata was 93.1 ± 8.1 (Structural and clinical outcomes after superior capsule reconstruction using an at least 6-mm thick autogenous fascia latas including the intermuscular septum). With a type I error rate of 0.05 (*α* = 0.05, two-tailed) and a power of 90% (*β* = 0.10), the sample size for the study protocol was calculated as 25 patients per group based on the primary outcome indicator by PASS 2021 (Power Analysis and Sample Size, NCSS, LLC, USA). Assuming a 15% drop-out rate, we plan to recruit 58 participants (29 per group) to the study.

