## Statistical methods

### Statistical methods for primary and secondary outcomes {20a}

The statistical software SPSS 25.0 was used for analysis. The normality of metric data, such as ASES scores, Constant scores, VAS scores, shoulder joint mobility, AHD, surgical duration, intraoperative blood loss, and postoperative drainage volume, was assessed using the Shapiro‒Wilk test and graphical analysis. Intergroup differences in metric data conforming to a normal distribution were evaluated using independent samples *t* tests, while nonnormally distributed metric data were assessed using the Mann‒Whitney *U* test. Count variables, such as the occurrence of complications, were evaluated for intergroup differences using the chi-square test. Paired samples *t* test was employed to assess intragroup differences in normally distributed metric data before and after surgery, while nonnormally distributed metric data were represented by median (interquartile range) and assessed using the Wilcoxon rank-sum test. Comparison of ordinal data, such as Hamada classification, Warner classification, Goutallier classification, and Sugaya classification, was conducted using the Wilcoxon rank-sum test. A *p* value less than 0.05 was considered statistically significant.

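### The 15% allowance for loss to follow-up protects precision but not against bias, and the per-visit tests at 6 to 24 months discard scores already collected from patients lost later

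*Protocol article*

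**What the plan says.** Section {20c} is headed as the place for methods to handle nonadherence and missing data. It has two sentences. The first relies on the retention strategies given earlier, such as combining study visits with routine clinic visits in {18b}. The second reads "The sample size is calculated to accommodate a loss to follow-up rate of 15% without affecting statistical power". Section {14} gives the matching number: "Assuming a 15% drop-out rate, we plan to recruit 58 participants (29 per group) to the study".

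Section {20a} fixes the comparison of the arms: "Intergroup differences in metric data conforming to a normal distribution were evaluated using independent samples" t tests, with a Mann-Whitney test for non-normal data. Section {20b} plans no further analyses.

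ASES and Constant scores are scheduled before surgery and at 3, 6, 12 and 24 months (section {12} and Table 1). The primary outcome paragraph lists all of these visits, while {18b} sets the primary evaluation at 3 months.

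**The concern.** A t or Mann-Whitney test at a visit can use only patients with a score at that visit. A patient scored before surgery and at 3, 6 and 12 months but missing at 24 months adds nothing to the 24-month comparison. The protocol does not call this a complete-case analysis, but that is what the named tests amount to when no other handling is stated.

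Recruiting extra patients restores the number of completers. It does not make them resemble the patients who left. If loss is related to how patients are doing, the late comparisons estimate the difference among those who stayed.

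Outcome-related loss is possible under the protocol's own rules. Section {16c} withdraws subjects who develop new health problems or cannot attend on time, and {22} removes patients with severe adverse events from the study.

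**Working it through.** **1. The plan's own figure.** Inputs from section {14}: "expected standard deviation (SD) of 5.8, a significance level at 5% and power of 0.90"; for SCR, "the score was 87.6 ± 5.8 at the latest follow-up"; the second published mean "was 93.1 ± 8.1 (Structural and clinical outcomes after superior capsule reconstruction". The planning difference is not stated; it is implied as 93.1 − 87.6 = 5.5. A two-sided 5% two-sample t test with difference 5.5 and SD 5.8 needs 25 per group (power 0.907), so the stated number reproduces.

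**2. Does the allowance preserve power?** 25 × 1.15 = 28.75, rounded up to 29 per group. After 15% loss, 29 × 0.85 = 24.65 per group remain. Power is 0.895 with 24 and 0.907 with 25. The power sentence therefore holds approximately under the plan's inputs.

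**3. Does it address bias?** The protocol gives no loss mechanism and no correlation between visits, so these are assumptions: SD 5.8, 15% overall loss before the later visit, loss driven by the earlier score (logistic, slope 1.5 per SD), and correlation between the two visits of 0.3, 0.5 or 0.7. The table shows the large-sample bias of the difference (STR minus SCR) among patients seen at the later visit, in ASES points.

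| Mechanism | 0.3 | 0.5 | 0.7 |
|---|---|---|---|
| Random loss | 0 | 0 | 0 |
| Low scorers lost in both arms, no true difference | 0 | 0 | 0 |
| Low scorers lost in both arms, true difference 5.5 | −0.2 | −0.4 | −0.6 |
| Low scorers lost in SCR, random loss in STR | −0.3 | −0.5 | −0.7 |
| Low scorers lost in SCR, high scorers in STR | −0.6 | −1.0 | −1.4 |

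In the third row the same rule removes about 22% of SCR and 8% of STR patients, because the SCR scores are lower. A regression that uses the earlier score brings the bias to about 0 in every row. None of these biases depends on the number recruited.

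Check: in the fourth row, loss raises the mean earlier score of the remaining SCR patients by about 1.02 points. The bias is minus the correlation times this shift: 0.3 × 1.02 = 0.31, 0.5 × 1.02 = 0.51, 0.7 × 1.02 = 0.71.

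A separate simulation with 29 per arm, loss after 12 months related to the score in SCR only, and correlation 0.5 to 0.8 gave biases of −0.4 to −1.1. This lies within the range above.

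**4. Scale.** SE = 5.8 × √(2/25) = 1.64. A bias of 0.2 to 1.4 points is 4% to 25% of 5.5, or 0.12 to 0.85 SE. With 25 per group and SD 5.8 unchanged, a true difference of 5.5 shifted by −0.5, −1.0 or −1.4 leaves power of about 0.85, 0.77 or 0.69.

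**5. Upper limit for one arm.** If exactly the lowest-scoring 15% of an arm were lost at the tested visit, lost patients and completers would differ by 5.8 × (0.2332/0.15 + 0.2332/0.85) = 10.6 points, where 0.2332 is the normal density at the 15% point. The bias would be 0.15 × 10.6 = 1.59 points.

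**The case against.** The strongest reply is that estimators for missing data and analysis sets usually belong in an SAP, and that {20c} never says incomplete patients are dropped. This would stand if the protocol were silent. It is not: {20a} names tests that cannot use earlier scores, {20c} answers remaining losses with a sample-size allowance, and {20b} excludes further analyses. The point is about the stated method.

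Several stronger readings are tempting, and the documents do not support them:

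- **That the power sentence is false, or that inflation is the only measure.** The sentence holds approximately, and {20c} also relies on retention.
- **That the primary result is at stake in the same way.** If 3 months is primary, as {18b} says, losses after that visit cannot affect it and only the preoperative score comes earlier. The argument applies mainly to 6 to 24 months.
- **That loss threatens a false claim for STR.** If poorly recovering SCR patients are lost, the shift is against STR. With no true difference, a shift of −0.5 or −1.0 lowers the chance of wrongly declaring STR better from 2.5% to about 1.2% or 0.5%; the extra rejections favour SCR. The opposite pattern of loss would reverse this, and nothing in the protocol says which to expect.
- **That the bias could reach 40% of the planning difference.** With loss in one arm this needs a gap of about 15 points between lost patients and completers (0.15 × 15 = 2.25). The limit under SD 5.8 and 15% loss is 10.6.
- **That equal loss rules are always harmless.** They are when the arms do not differ, but not when the planned 5.5 points is real.
- **That differential loss is to be expected from the cited retear rates.** The background says "Retear rates were seen with partial cuff repairs (45%), graft interposition (21%) and SCR (21%), respectively". It gives none for STR and does not link retear to loss.

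It also stands that a mixed model is one of several acceptable choices.

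**Conclusion.** The point holds as a worthwhile improvement, not as a fatal flaw. As written, the later comparisons of ASES and Constant are complete-case and ignore scores that the schedule already collects. The allowance protects precision and leaves bias open. The size, about 0.2 to 1.4 ASES points against 5.5, rests entirely on the assumed loss mechanisms and correlations. Using the earlier scores removes this bias only if loss is explained by observed data. At a 3-month primary visit the benefit is mainly baseline adjustment.

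**What to change.** - In {20a} and {20c}, make the between-group analysis of ASES and Constant a mixed model for repeated measures with arm, visit, arm-by-visit and preoperative score. Use all postoperative scores of all randomised patients who have an irreparable tear and received surgery, analysed as allocated.
- Read the arm difference at the stated primary visit. The primary outcome paragraph and {18b} must first be reconciled on which visit that is.
- Add one sensitivity analysis that shifts the imputed scores of lost patients by arm, in either direction, to show how large a departure would change the conclusion.
- State in {20c} that the 15% allowance protects precision only.

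The cost is wording and slightly more analysis work; no new visits, data or patients are needed. The downside is reliance on a missing-at-random assumption, which the sensitivity analysis examines. The proposed population still leaves out patients whose tear is found repairable in theatre, whom {11b} already takes off the allocated treatment, so their number should be reported by arm.

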### Plans to give access to the full protocol, participant-level data and statistical code {31c}

No longer than 5 years after the collection of the 2-year post-randomization interviews, only the main project principal will deliver a completely deidentified dataset to an appropriate data archive for sharing purposes.

## Oversight and monitoring

### Composition of the coordinating centre and trial steering committee {5d}

The study will be performed by the Sports Medicine Center at Southwestern Hospital. There is no other coordinating centre. The trial steering committee consisted of the ethics committee of the First Affiliated Hospital of Army Medical University (No. AKY2022126) and the clinical research team. The research team consists of two principal investigators who oversee the study and are responsible for medical responsibilities, a study coordinator who plans patient visits, and an investigator who is responsible for data management and trial management. The research team meets weekly to assess progress, identify potential test subjects and work out logistical issues. A statistician was involved in the design of the trial and consulted on statistical issues throughout the study. Study leader [name] identified the enrolled patients in the outpatient department. A researcher collected general patient information. To improve the reliability of the test and reduce the differences between operators, the following measures were taken: All the operations were led by [name], and all the operations were photographed and recorded by video. The test data were evaluated and counted by one person.

### Composition of the data monitoring committee, its role and reporting structure {21a}

Medical records, registration names, and special clinical observation record data, including doctors’ clinical medical records, are used in this study.All data and records relating to clinical observations are kept in the investigator or clinical trial medical facility and made directly accessible to the originator of the clinical trial or the person in charge of the competent authority;Clinical observation investigators are responsible for preserving the relevant data collected. No one other than members of the study group, ethics committees, or medical regulators will have access to the data collected in this study without good reason.

### Adverse event reporting and harms {22}

Management of adverse events: When mild adverse events occur, the investigator should treat them actively and according to surgical management principles without terminating the trial. For severe adverse events, in addition to active rescue, the trial should be terminated and unblind to the rescuer and participants. The observation and follow-up will be continued; however, it will be removed from the study. The investigator should report to the subject leader within 24 h, timely report to the ethics committee, and record the adverse event in the CRF form. All adverse events should be followed up until remission or stabilization. If the patient dies, the patient should be removed from the list of study participants.

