### Procedure for unblinding if needed {17b}

Because a surgical procedure is involved, the surgeons including the principal investigator were unblinded to the trial, and the evaluators collecting outcome data did not join the operation and were blinded throughout the study. When there is serious adverse event reporting and harms or the trial is finished, it will be unblinded.

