#### Adverse event management

Adverse event recordAdverse events: various surgical complications;Serious adverse events: events that require or prolong hospitalization, cause disability, affect the patient’s working ability, endanger the patient’s life cause death, and lead to congenital malformations during the course of the clinical trial.Adverse event report

Management of adverse events: When adverse events occurred, the investigator should treat them actively and according to surgical management principles without terminating the trial or discontinuing the follow-up. For serious adverse events, in addition to active rescue, the experiment should not be terminated, and observation and follow-up should be continued. The investigator should report to the subject leader within 24 h, timely report to the ethics committee, and record the adverse event in the CRF form. All adverse events should be followed up until remission or stabilization. If the patient dies, a new patient can be enrolled.

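### Contradictory adverse-event rules, one of which removes randomised patients from the study after surgery for reasons that can be related to outcome

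*Protocol article*

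**What the plan says.** Two sections of the protocol article give rules for the same situation.

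- **Adverse event management** (under Data collection and management) sets a general rule that adverse events are treated "without terminating the trial or discontinuing the follow-up". It defines serious events broadly, including "events that require or prolong hospitalization, cause disability", effects on working ability, and death. It then says: "For serious adverse events, in addition to active rescue, the experiment should not be terminated, and observation and follow-up should be continued". On death: "If the patient dies, a new patient can be enrolled".
- **Adverse event reporting and harms {22}** contrasts mild with severe events. It says: "For severe adverse events, in addition to active rescue, the trial should be terminated and unblind to the rescuer and participants". It continues: "The observation and follow-up will be continued; however, it will be removed from the study". On death, "the patient should be removed from the list of study participants".

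Two further sections bear on the point. **Procedure for unblinding if needed {17b}** says: "When there is serious adverse event reporting and harms or the trial is finished, it will be unblinded". **Implementation {16c}** lists grounds on which subjects are asked to withdraw. They include new health problems during the study and failure to cooperate with treatment or to attend visits on time.

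**The concern.** An investigator whose patient is readmitted with a deep infection cannot follow both sections. One keeps the patient in the trial; the other takes the patient out.

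The second rule is also harmful in itself. It acts after randomisation and surgery, and it is triggered by events that can reflect how the operation performed. Other evaluation names infection and retear among the recorded adverse events, and either becomes serious if it leads to hospitalisation or disability. Removing such patients leaves a selected, better-scoring remainder in each arm. If the two operations differ in how often or how badly they fail, STR versus SCR is biased, and the direction cannot be known beforehand. The {16c} grounds work the same way. Events still go into the case report form, so the main risk is to the efficacy comparison.

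Exposure depends on when the primary outcome is measured. Plans to promote participant retention {18b} places it at 3 months; Primary outcome lists 3, 6, 12 and 24 months. If 3 months governs and recorded scores are kept, only removals before then affect it. If it runs to 24 months, later removals count too.

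**Working it through.** **1. The rules side by side**

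| | Adverse event management | Adverse event reporting and harms {22} |
|---|---|---|
| Term | serious (defined) | severe (undefined, contrasted with mild) |
| Participation | not terminated | terminated; case removed |
| Blinding | silent | rescuer and participant unblinded |
| Observation | continues | continues |
| Death | new patient may be enrolled | struck from the participant list |

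Reading the two terms as one category is an inference. It rests on shared content (active rescue, report within 24 h, ethics committee, case report form, follow-up to stabilisation) and on {17b}, which attaches to serious events the unblinding that {22} attaches to severe ones. The death rules do not contradict each other, but each takes a randomised patient out.

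**2. The plan's own sample size**

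Inputs from Sample size {14}: means 93.1 and 87.6, so a difference of 5.5; SD 5.8; two-sided 5%; power 90%.

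n = 2(1.960 + 1.282)² × (5.8/5.5)² = 23.4, so 24 per arm. The t-test version gives 24.4, so 25, which reproduces the plan. The stated 29 per arm is 25 × 1.15 = 28.75, rounded up.

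**3. Size of the effect (illustration)**

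The document gives no serious-event rate, so the removed share p and the deficit d are assumptions. If a share p of an arm is removed and those patients would have scored d points below the rest of that arm:

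- the arm mean rises by p × d;
- the SD becomes √(5.8² − p(1−p)d²);
- n becomes n₀(1−p).

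Starting sizes are n₀ = 25 (removals on top of the full 15% drop-out, 29 × 0.85 = 24.65) and n₀ = 29 (no other drop-out). The test is a two-sided 5% Welch t test.

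Worked case: d = 10, SCR loses 7%, STR 3.5%, n₀ = 25.

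- SCR: mean +0.70; SD √(33.64 − 6.51) = 5.21; n = 23.25.
- STR: mean +0.35; SD √(33.64 − 3.38) = 5.50; n = 24.1.
- Observed difference: 5.5 + 0.35 − 0.70 = 5.15, a shift of 0.35 (0.35/5.5 = 6%).
- Standard error: √(30.26/24.1 + 27.13/23.25) = 1.556; noncentrality 5.15/1.556 = 3.31; power 90.0%.

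In the table each pair is for n₀ = 25 / 29. Power assumes a true difference of 5.5. The false-positive rate assumes none and counts rejections in either direction.

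| Removed, SCR v STR | d | Shift | Power | False-positive rate |
|---|---|---|---|---|
| none | – | 0 | 90.7% / 94.4% | 5.0% |
| 7% v 3.5% | 5 | 0.175 | 88.3% / 92.6% | 5.1% / 5.1% |
| 7% v 3.5% | 10 | 0.35 | 90.0% / 93.8% | 5.6% / 5.7% |
| 3.5% v 7% (reverse) | 10 | 0.35 | 95.7% / 97.8% | 5.6% / 5.7% |
| 14% v 7% | 10 | 0.70 | 88.9% / 93.1% | 7.5% / 7.9% |
| 7% v 0% | 10 | 0.70 | 84.2% / 89.3% | 7.2% / 7.5% |
| 21% v 0% | 10 | 2.10 | 60.9% / 67.6% | 28% / 32% |

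Of 29 patients, 3.5%, 7%, 14% and 21% are about 1, 2, 4 and 6. Equal shares with equal deficits give zero shift and a 5.0% false-positive rate.

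A simulation of 8,000 trials with the planned t test (7% v 3.5%, d = 10) agrees. Power is 89.8% / 93.2% with removal and 90.3% / 94.3% with everyone kept. The false-positive rate is 5.1–5.8% with removal and 4.7–5.2% without, against a simulation error of about √(0.05 × 0.95/8000) = 0.24 points.

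**The case against.** **Serious and severe are different scales.** One concerns consequence and the other intensity, and no section equates them. That is a fair reading of the words, but it does not remove the conflict. The general rule in Adverse event management covers adverse events of any kind and forbids terminating on their account, so ending participation for a severe but non-serious event still breaches it.

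**Removal does not say that scores are discarded.** This is true, and {22} continues follow-up. Which recorded scores enter the analysis is normally settled in an analysis plan, which may exist. Loss from the comparison is therefore the natural reading of removal, not a stated rule. However, the removal instruction is stated, and a patient who withdraws under {16c} may supply no later data for an analysis plan to use.

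**The numbers are small.** In the moderate case they are: 5.0% to 5.6% is hard to separate from simulation error. Power is also a poor gauge of bias here, because removing low scorers shrinks the SD. That is why a 5-point deficit gives lower power than a 10-point one, and why power rises when STR loses more. With no deficit at all, removing 7% v 3.5% gives 89.1% at n₀ = 25, so about 1.6 of the 2.4-point fall in the 5-point case is lost numbers alone. The shift in the difference and the false-positive rate are the better measures.

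**The death and {16c} rules add little.** A patient who dies has no later scores either way, and dropping the non-cooperation ground recovers nothing from missed visits. Both points are largely right. What remains is the possible loss of earlier scores, a blurred safety record, and withdrawal of patients who could still have attended.

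**Conclusion.** The concern holds. The two sections give incompatible instructions for a patient with a grave adverse event. Followed as written, {22} and {16c} take randomised patients out after surgery for reasons that can be tied to outcome. This is a fault in stated rules, not something left to an analysis plan.

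Confidence is high on the contradiction and lower on the amount of bias. With a 10-point deficit and one to four patients removed per arm, unevenly, the difference shifts by 0.35 to 0.70 points (6% to 13% of 5.5) and the false-positive rate reaches 5.6% to 7.9%. The effect is large only if about six patients are lost from one arm and none from the other. The document gives no basis for that: Background cites a 21% retear rate for SCR, but not every retear would be serious and no STR rate is given. The direction is unknown. The point should be fixed, but it does not by itself undermine the trial.

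**What to change.** Amend the protocol as follows.

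1. Delete the removal rules in Adverse event reporting and harms {22}, the replacement rule in Adverse event management, and the new-health-problems and non-cooperation grounds in Implementation {16c}.
2. State one rule: every randomised patient confirmed irreparable at surgery (Eligibility criteria {10} and Criteria for discontinuing {11b}) stays in the assigned arm, is followed to 24 months unless consent is withdrawn, and is analysed as allocated.
3. Make unblinding a per-patient step that does not end follow-up.
4. Report serious events and deaths by arm, neither deleted nor replaced. Keep scores recorded before a death; the analysis plan can say how later ones are treated.
5. Use one term, *serious*, as already defined, in {17b}, {22} and Adverse event management.

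Clinical management of the event stays with the investigators. Confirmation of irreparability is itself decided after randomisation, by surgeons who know the allocation. This fix leaves that feature of the design as it is.

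The cost is one amendment. It adds no visits beyond the existing schedule, and {22} already continues follow-up of these patients. The price is somewhat more variable scores, because patients with complications stay in.
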